### Plans to give access to the full protocol, participant level-data and statistical code {31c}

The full protocol, participant-level dataset, and statistical code can be requested from the principal investigator.

### Oversight and monitoring

#### Composition of the coordinating center and trial steering committee {5d}

The composition of the trial steering committee at the coordinating center exists of two PhD students from the coordinating center who are responsible for the day-to-day logistics of the trial, including identification of eligible patients, patient inclusion and randomization, and arranging follow-up appointments for patients randomized for the intervention arm. Additionally, they are supervised by an assistant professor and the principal investigator, with whom they meet on a weekly basis and can be consulted for discussion. The coordinating center is responsible for the correct coordination of the trial and providing oversight over all participating centers. The steering committee is assisted by clinicians from the coordinating center (i.e., the Regional Academic Cancer center Utrecht; RAKU), who are involved in the care of pancreatic cancer patients and are present at multidisciplinary team meetings, including surgeons, medical oncologists, radiation oncologists, radiologists, gastroenterologists, and pathologists, are easily accessible for consultation and support.

At each participating center, the local investigator is responsible for the on-site logistics and will appoint an appropriate trial team, which can in part be delegated to the coordinating center. Members of the DPCG will be updated on the trial progress at least during the four yearly DPCG meetings, but can be contacted for consultation, if needed. Radiologists from the participating expert pancreatic cancer center will revise all follow-up CT scans of patients who underwent surgery in their center, if performed elsewhere. In case recurrence is detected, this will be discussed at a multidisciplinary team meeting, functioning as an expert panel for determining study endpoints. Data managers from the coordinating center are responsible for data management, together with the daily trial coordinators.

### Composition of the data monitoring committee, its role, and reporting structure {21a}

The independent Data Safety Monitoring Board (DSMB) will consist of [name]. [name], epidemiologist/statistician, Dr. [name], Dr. [name], and Dr. [name]. The DSMB will meet once yearly and will review the progress and accruing data of this trial and provide advice on the conduct of the trial to the Trial Steering Committee. The role of the DMSB will be to perform an interim review of the trial’s progress including updated figures on recruitment, data quality, and main outcomes and safety data.

### Adverse event reporting and harms {22}

Adverse events in the intervention arm are assessed and recorded by the local investigator and, if necessary, discussed with a radiologist or surgeon. The following aspects will be recorded for each event:description and grade of the toxicity according to the Common Terminology Criteria for Adverse Events (CTCAE) version 5.0 [35];date of onset;date of recovery;action taken (intervention);outcome of the adverse event.

The sponsor will report serious adverse events in the intervention arm through the web portal *ToetsingOnline* to the accredited medical research ethics committee (MREC) (in Dutch: medisch ethische toetsing commissie, METC) that approved the protocol, within 7 days of first knowledge for serious adverse events that result in death or are life threatening followed by a period of maximum of 8 days to complete the initial preliminary report. All other serious adverse events will be reported within a period of maximum 15 days after the sponsor has first knowledge of the serious adverse event. As PDAC patients have a very poor prognosis, we expect that many patients suffer from follow-up unrelated SAEs within the 2-year study period. These SAEs will be recorded, although not reported. Adverse events will be followed until they have abated or until a stable situation has been reached. Depending on the event, follow-up may require additional tests or medical procedures as indicated and/or referral to the general physician or a medical specialist. Serious adverse events need to be reported until the end of the study within the Netherlands, as defined in the protocol. As the control arm of the trial is treated according to current standard of care, adverse events in the control group will not be reported.

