	Benefit of imaging is unclear; it seems to result in greater detection of asymptomatic recurrence	
	Primary focus on treatment-related toxicity, survivorship issues, and recurrence monitoring	
National Dutch Guideline Pancreatic carcinoma (NVvH—2019) [15]	Clinical follow-up. In case of symptoms of disease recurrence, additional diagnostic testing can be used	Uniform expert opinion (2A)
	Consider routine diagnostic follow-up in an investigative context only	Low (C)
International Association of Pancreatology/European Pancreatic Club (IAP/EPC—2016) [16]	No recommendation	Not applicable

Recent introduction of more potent systemic therapies, such as fluorouracil, leucovorin, irinotecan and oxaliplatin (FOLFIRINOX) and gemcitabine/nab-paclitaxel combination therapy, and local ablative therapies, such as stereotactic body radiation therapy (SBRT), has opened the field for treatment of PDAC recurrence [4, 17]. Despite a lack of evidence, this has resulted in an increased interest in recurrence-focused postoperative surveillance with routine imaging and serial serum tumor marker testing, with the ultimate goal to detect PDAC recurrence at an early asymptomatic stage [18]. This hypothetically leads to the identification of patients with a good performance status who are most likely to tolerate (experimental) treatment [19]. However, it remains unclear whether all patients with asymptomatic PDAC recurrence can be treated and whether early initiation of recurrence-focused treatment results in improved oncological outcomes. Moreover, early initiation of recurrence treatment in asymptomatic patients might induce treatment-related toxicity, which could worsen quality of life. Recurrence-focused surveillance could also increase fear of cancer recurrence, which negatively impacts quality of life, as might detection of recurrence in an asymptomatic stage [20, 21]. Consequently, in most European countries including the Netherlands and the United Kingdom (UK), ethical concerns towards a recurrence-focused follow-up are raised and guidelines do not recommend a recurrence-focused follow-up strategy [11, 14].

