#### Recurrence diagnosis

If disease recurrence (local and/or distant) is suspected on the basis of a follow-up CT scan, with or without elevated tumor markers, pathological confirmation is strongly advised. If the results remain inconclusive or pathology cannot be obtained, additional imaging (magnetic resonance imaging (MRI) and/or positron emission tomography CT (PET-CT)) may be considered. Consensus on the presence of a recurrence should be obtained in a multidisciplinary meeting (e.g., based on imaging, elevated CA 19–9, and clinical evaluation).

If disease recurrence is diagnosed, best supportive care (BSC) or systemic and/or local therapy is offered at the discretion of the treating clinician in both trial arms, which is the current standard practice, and trial-related follow-up will end. It is encouraged to offer treatment to all patients in whom there are no contraindications based on clinical condition (performance status), comorbidity, or specific exclusion criteria for systemic and/or local therapy. Patients can be offered to participate in intervention trials on management of pancreatic cancer recurrence. In the Netherlands, within the DPCG, two intervention studies for the treatment of PDAC recurrence have been simultaneously initiated: the ARCADE trial (NCT04881487), investigating the efficacy of stereotactic body radiation therapy on survival after recurrence and quality of life in patients with isolated local PDAC recurrence, and the TIMEPAN trial (NCT04897854) studying the optimal timing of start of systemic treatment for asymptomatic metastasized PDAC.

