### Outcomes {12}

The primary outcome is overall survival, defined as the time from the date of PDAC resection until the date of either death from any cause or last follow-up.

Secondary outcomes are the following:Patient-reported quality of life and worry of cancer recurrence, as measured by PROMs questionnaires within the PACAP-PROMs and PACOPS project: general EORTC QLQ-C30 and EQ5D-5L, pancreas-specific EORTC QLQ-PAN26, HADS, and WOPS.Compliance to recurrence-focused surveillance, measured as the percentage of patients that either accepts or refuses participation in the intervention-arm, i.e., is willing to undergo recurrence-focused follow-up.Disease-free survival, defined as the interval between the date of PDAC resection and the date of first radiological signs of recurrence, or last follow-up if recurrence is not observed. Preferably, recurrence is proven by a biopsy showing pathological confirmation of recurrent PDAC. However, recurrence can be clinically confirmed with growth of a suspicious lesion on consecutive CT scans and elevation of CA 19–9 (> 37 U/ml) and/or activity on PET-CT following consensus in a multidisciplinary meeting.Clinical and radiological patterns of disease recurrence:◦ Asymptomatic recurrence is defined as PDAC recurrence detected by CT imaging during follow-up, in the absence of suspected symptoms. If PDAC recurrence is discovered due to a significant patient-initiated complaint that is new or has been increased in severity or frequency, disease recurrence is defined as symptomatic.◦ Localization of recurrence is categorized using five categories: (1) isolated locoregional recurrence: recurrence in the pancreatic remnant, locoregional lymph nodes, or surgical bed, such as soft tissue along the celiac or superior mesenteric artery, aorta, or around the pancreatojejunostomy site; (2) isolated distant recurrence: recurrence restricted to a single organ or site; (3) local + distant recurrence: simultaneous occurrence of both isolated locoregional recurrence and isolated distant recurrence; (4) multiple recurrence: recurrence at multiple distant sites; and (5) peritoneal carcinomatosis.The yield of CT surveillance and role of serum tumor marker testing in detecting PDAC recurrence, by calculating diagnostic accuracy values, i.e., sensitivity, specificity, positive predictive values, and negative predictive values.Eligibility for additional (experimental) treatment at time of recurrence diagnosis, based on the Eastern Cooperative Oncology Group (ECOG) or Karnofsky performance state, or inclusion criteria for study-related treatment of recurrence.Reasons to refrain from treatment for recurrence (i.e., non-eligibility, deteriorated condition, patient’s wish, doctors’ advice, progression during treatment, etc.).Patients’ tolerance to treatment for recurrence, measured by the reasons to stop treatment for recurrence (i.e., per protocol, deteriorated condition, patient’s wish, doctors’ advice, progression during treatment etc.).Morbidity associated with recurrence-focused treatment.Overall costs of recurrence-focused surveillance vs. costs as incurred with current non-standardized follow-up. Cost-effectiveness is examined through the EQ5D questionnaire and calculated using a Markov model.

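### Morbidity of recurrence treatment is a secondary outcome in a trial that treats recurrence in both arms, but the only toxicity recording described covers the intervention arm

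*Protocol article*

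**What the plan says.** Outcomes {12} includes, as an item separate from tolerance, "Morbidity associated with recurrence-focused treatment". It gives no measure, grading, time window or data source for that item. The Recurrence diagnosis subsection has supportive care or systemic and/or local therapy offered at the clinician's discretion in both arms. It adds that at this point "trial-related follow-up will end".

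Adverse event reporting and harms {22} opens with "Adverse events in the intervention arm are assessed and recorded by the local investigator" and goes on to CTCAE v5.0 grade, dates of onset and recovery, action taken and outcome. On serious events unrelated to follow-up it says "These SAEs will be recorded, although not reported". It closes by stating that, because controls receive standard care, "adverse events in the control group will not be reported".

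The Background explains why toxicity matters for this question: "early initiation of recurrence treatment in asymptomatic patients might induce treatment-related toxicity".

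**The concern.** Surveillance is expected to work by finding recurrence earlier and so leading to more treatment. The toxicity of that treatment is the other side of the same mechanism, and the Background names it as a possible harm. A morbidity outcome informs that balance only if events are found in the same way in both arms.

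The harms section describes structured, graded recording in one arm and nothing comparable in the other. If the morbidity outcome is filled from what is described, there are two likely results. Either the intervention arm is reported alone with no comparator, or its graded events are set against whatever routine notes hold for controls. In the second case the arms differ in how hard anyone looked, and a difference in rates cannot be separated from a difference in ascertainment.

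**Working it through.** No arithmetic applies. The article gives no morbidity rate, no figure for the proportion of recurrences treated, and no planned test for this outcome. The check sets the statements side by side.

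1. **Is the outcome relevant to both arms?** Yes. Recurrence treatment is offered in both arms (Recurrence diagnosis), and the trial's question is a contrast between arms.

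2. **What toxicity recording is described?** Only that in the harms section {22}, and its recording sentence names the intervention arm. Nothing there provides for recording in controls. Who will be blinded {17a} adds that controls and their treating clinicians are not further notified, so prospective trial grading by those clinicians is unlikely.

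3. **Does the stated reason fit this outcome?** Controls are exempted because they receive standard care. The Recurrence diagnosis subsection describes clinician-directed recurrence treatment, in both arms, as current standard practice. For treatment morbidity the reason therefore applies equally to the intervention arm and does not support a difference between arms.

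4. **Does the recording reach the relevant period?** Trial-related follow-up ends when recurrence is diagnosed, which is when the morbidity in question begins. The article does not say whether intervention-arm adverse event recording continues beyond that. If it does, structured data exist in one arm only. If it does not, no toxicity source is described for either arm during recurrence treatment.

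5. **Is another source named?** Trial design {8} has the cohorts collecting clinical, laboratory and radiological findings before, during and after treatment, and controls are followed there. This could supply the data, but adverse events and grades are not mentioned and the morbidity outcome is not tied to it. Statistical methods {20a} lists tolerance among the descriptive analyses and does not mention morbidity.

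6. **Direction of any bias.** If intervention-arm events are actively assessed and graded while control events come from routine notes, more events will tend to be found per treated patient in the intervention arm even when true toxicity is equal. That would overstate the harm of surveillance.

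7. **Who is affected.** At most 153 controls are planned (Sample size {14}), but only those who recur and then receive treatment can contribute. Supportive care alone is one of the options, so the number is below 153 and cannot be derived from the article.

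**The case against.** Several points on the other side are sound and set the limits of this finding.

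- **Tolerance.** A reader might infer that tolerance of recurrence treatment also cannot be compared. It can. Outcomes {12} measures it by reasons for stopping and Statistical methods {20a} by completion as planned. Neither depends on adverse event recording.
- **Recorded versus reported.** A reader might infer that control-arm events are certainly not collected. The closing sentence says only that they are not reported, and the same section treats recording and reporting as different things: "These SAEs will be recorded, although not reported". Intervention-only recording is a fair inference from the opening sentence but is not stated outright.
- **Data after recurrence.** A reader might take "and trial-related follow-up will end" to mean that all data stop. They do not. Provisions for post-trial care {30} keeps patients enrolled for up to 2 years and follows survival until death. The analyses of post-recurrence survival, treatment type and time to treatment start all need later data.
- **Weighing benefit against harm.** A reader might conclude that a survival result could not be weighed against harm at all. Quality of life is measured in both arms with five questionnaires and compared by mixed model, and the Discussion calls it the most important secondary endpoint. It captures part of the toxicity burden, though not graded events.
- **The DSMB.** The board reviews "main outcomes and safety data". The article does not say that it sees one arm only.
- **Condensation.** The full protocol and its case record form are not shown and may define the morbidity outcome.

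The last point answers the missing definition taken alone. It does not answer the rule that the article does state, which limits the described recording to one arm while the outcome concerns treatment given in both. Not sending control-arm serious events to the ethics committee is reasonable and is not criticised here.

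**Conclusion.** The point holds for one secondary outcome. Followed as written, the article gives no symmetric basis for comparing recurrence-treatment morbidity between arms, and the most readily available comparison would carry differential ascertainment. It does not show that such a comparison is impossible, since cohort data or an unseen case record form could support one.

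The size cannot be quantified from the document. The outcome affected is secondary, and the controls concerned are those who recur and are treated. Overall survival, tolerance and quality of life are not affected. The conclusion rests on two assumptions: that the morbidity outcome is meant to inform the contrast between arms, which the article implies but for which it names no test, and that the recording described in the harms section is the trial's main source of toxicity data. It is a cheap improvement worth making before analysis, not a threat to the trial's main result.

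**What to change.** Leave expedited serious adverse event reporting to the ethics committee unchanged. For the morbidity outcome:

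- Define one measure, grading, time window and data source, identical in both arms. An example is severe CTCAE v5.0 events and unplanned admissions during recurrence treatment, abstracted from the medical record through the cohort case record form. Use this source for the intervention arm too, even where prospectively graded events exist.
- State that this collection continues after trial-related follow-up ends at recurrence.
- Compare by randomised arm. Receiving recurrence treatment may itself depend on allocation, so a comparison among treated patients only would lose the protection of randomisation.
- Reconcile the Recurrence diagnosis, Outcomes {12} and harms {22} sections accordingly, and align the two wordings of tolerance in Outcomes {12} and Statistical methods {20a}.

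Controls need not be contacted, because the consent described in Trial design {8} and in section {26b} covers use of their medical data. The final analysis is planned 30 months after the last enrolment (Recruitment {15}), which leaves time for abstraction. The cost is protocol wording, some case record form fields and modest data entry, including retrospective abstraction for patients already treated. Chart-based grading is less complete than prospective grading, but the incompleteness should be similar in the two arms.

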### Frequency and plans for auditing trial conduct {23}

To assure quality and validity of research data, an independent, qualified monitor is appointed to monitor the study procedures. Monitoring is performed according to the Nederlandse Federatie van Universitaire Medische Centra (NFU) guidelines. During monitoring, the inclusion rate, study files, informed consent, in- and exclusion criteria, data review and data verification, serious adverse events, research procedures, research data, and research equipment will be checked for a random sample of patients. The risk of the study is classified as “negligible,” and minimal monitoring is therefore needed. Minimal monitoring exists of an initiation visit for each participating center, at least two on-site visits in the coordinating center (depending on the trial duration, the number of study participants and observed deviations), and a closing visit. At any given point during the study, the trial can be selected for audit. There is no predefined schedule for audits and inspections.

### Plans for communicating important protocol amendments to relevant parties (e.g., trial participants, ethical committees) {25}

Amendments are changes made to the research after a favorable opinion by the accredited MREC has been given. All amendments will be notified to the MREC that gave a favorable opinion.

### Dissemination plans {31a}

To disseminate the knowledge obtained, we will report the results from this project in one or more manuscripts, which will be submitted to high-impact, peer-reviewed journals. Results will also be discussed at regular meetings of the DPCG, and other national and international meetings, and will be submitted for presentation to (inter)national conferences. Also, the results may be included in treatment guidelines for PDAC.

## Discussion

The RADAR-PANC trial investigates whether a recurrence-focused surveillance strategy with serial tumor marker testing and routine imaging improves overall survival in patients after radical (R0/R1) resection of PDAC in the Netherlands, compared to current, non-standardized follow-up. Furthermore, the consequences of a recurrence-focused surveillance strategy on quality of life and recurrence-focused (experimental) treatment are assessed.

The impact of recurrence-focused surveillance has been prospectively investigated in patients who received treatment for other cancer types, including colorectal cancer and epithelial ovarian cancer. These studies did not demonstrate a disease-specific survival benefit of multimodality surveillance with a certain interval and cost-effectiveness of a recurrence-focused surveillance strategy remained unclear [36–39]. Unfortunately, the risk of disease recurrence after PDAC resection is substantially higher than for other cancer types. If timely treatment of disease recurrence in PDAC patients leads to improved survival, recurrence-focused follow-up might be more beneficial for these patients. Given that prospective studies on this subject are lacking, conclusions about the potential advantages of recurrence-focused surveillance after PDAC resection cannot be made. The RADAR-PANC trial will be the first randomized controlled trial to generate high level evidence for the current clinical equipoise regarding the value of recurrence-focused postoperative surveillance with serial tumor marker testing and routine imaging in patients after PDAC resection.

During the initiation of this study, several issues have been debated. First of all, the main study endpoint has been an important subject of discussion. Clearly, recurrence-focused surveillance alone does not lead to improved survival. Early recurrence detection following recurrence-focused surveillance, however, holds the potential to increase the eligibility for early initiation of recurrence-focused treatment, which might be associated with survival benefits. The efficacy and optimal timing of recurrence treatment has not been studied extensively and remains a subject of discussion. As a consequence, recommendations on treatment for recurrence are lacking in current PDAC guidelines [15]. Considering that the RADAR-PANC trial may lead to the detection of recurrence before the onset of symptoms in a substantial part of patients, discussions were held on how to treat patients with asymptomatic disease recurrence. The potential survival benefits of recurrence-focused postoperative surveillance are anticipated to result from early initiation of recurrence treatment. It was therefore decided that all patients in whom disease recurrence is diagnosed should be offered (experimental) treatment or participation in a clinical intervention trial. Within the Netherlands, the DPCG has simultaneously initiated two randomized controlled trials on respectively the optimal timing of systemic therapy for patients with disseminated disease, i.e., the TIMEPAN trial (NCT04897854), and the efficacy of SBRT for the treatment of isolated local PDAC recurrence in addition to standard of care, i.e., the ARCADE trial (NCT04881487). Nevertheless, while it is strongly encouraged to offer all trial participants treatment at time of recurrence diagnosis, type, and timing of treatment will be determined through shared decision-making. This might reduce the potential survival benefits of recurrence-focused surveillance, although insights into the impact on patients’ quality of life will be obtained.

In addition, it was discussed whether the main endpoint should be overall survival, defined as the interval between the date of resection and the date of death, or post-recurrence survival, defined from the date of recurrence diagnosis until date of death. The date of recurrence diagnosis, however, is highly dependent on the applied surveillance strategy and post-recurrence survival will therefore be subjected to lead time bias. Another outcome that was taken into consideration as potential main endpoint was quality of life. One of the most important reasons to refrain from recurrence-focused surveillance is the negative impact it might have on the quality of life of patients with an already poor prognosis. Nevertheless, a sample size can be calculated more reliably by using a hard endpoint such as survival instead of a soft outcome as quality of life. We therefore decided to make quality of life the most important secondary endpoint. In addition, this will be the first study to investigate the impact of a recurrence-focused surveillance strategy on the quality of life of patients after PDAC resection. As previous studies and relevant numbers on this subject are lacking, a proper sample size calculation with quality of life as main study endpoint could not be performed.

Lastly, the use of the TwiCs design has been extensively discussed. TwiCs is an innovative study design that has been proposed by Relton et al. in 2010 as a potential solution for certain logistical challenges in traditional randomized trials [23]. Theoretical advantages of TwiCs include efficient patient recruitment, considering that an observational patient cohort is used as multiple trials facility, which also leads to increased generalizability of results (less selection bias), and efficient use of routinely collected data [22]. The two-staged, patient-centered informed consent procedure is specifically chosen to prevent disappointment bias and contamination [25]. Especially in the setting of a trial on recurrence-focused postoperative surveillance, recruitment in a traditional RCT would be challenging, given that patients who have been informed about the potential benefits of surveillance may not be willing to accept randomization. In setting-up the RADAR-PANC trial, however, ethical concerns with regard to the TwiCs design were raised by some of the involved pancreatic cancer clinicians. It was questioned whether it was ethically acceptable that patients who are randomized to the control arm of the trial are not explicitly notified about their trial participation. At cohort enrolment, however, patients are well informed that they can be serving as control without further notifications. In addition, a survey among cancer patients who served as control in previous TwiCs showed that the majority of patients considered this to be acceptable [26]. Nevertheless, explanation to and education of researchers and physicians is of great importance to overcome ethical dilemmas.

